## 17.3 Analysis

### 17.3.1 Inclusion of participants in the analysis

Participants will be included in the modified intention-to-treat analysis if they satisfied all the entry criteria and received the study intervention (screening by RDT or dose of SP) on at least one occasion, with no other exclusions. Women who give consent to enter the study but withdraw the same day and did not receive any study intervention (RDT or SP) will be classed as screening failures and not included in the analysis (e.g. in ongoing trials a few women gave consent, but then changed their mind during the same visit prior to, or during the study enrolment procedures).

Participants will be included in the per-protocol analysis if they satisfied all the entry criteria and either received the study intervention (IPTp-SP or ISTp-DP) on at least three separate occasions at least four weeks apart; or reached a study end-point before completion of the three-visit schedule but received the intervention at least once; or received an approved alternative treatment for symptomatic malaria according to protocol that replaced the need for the scheduled intervention. Participants who received the study medication but were reported not to have adhered to treatment (defined as taking at least 2/3 of the recommended dose over the recommended time period, on each occasion that treatment is required) or who used prohibited medication will be excluded from the per-protocol analysis. Women who were HIV negative at enrolment but HIV positive by the third trimester will be excluded from the per-protocol analysis.

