#### **7.2.6 Inclusion of women treated for malaria and anaemia**

Women with symptoms of malaria at enrolment will not be excluded, but will be randomized to the study groups, and treated with the case-management drug, artemether-lumefantrine (CoArtem) if they fall in the IPTp-SP group. They will not receive SP that month, because lumefantrine is anticipated to provide post-treatment prophylaxis comparable with SP (3 to 4 weeks), based on recently completed treatment studies in pregnant women in Uganda. SP will then be provided at the next scheduled visit. Women randomized to the ISTp arm will already receive DHA-PQ as the treatment drug. DHA-PQ and CoArtem have comparable efficacy in treating malaria.

Women participating in the trial will receive all usual routine antenatal care, and will also be encouraged to attend the clinic if they feel unwell between appointments. As part of this package of care, women attending with symptoms consistent with malaria or anaemia will be tested and treated as appropriate, and continue in the study. No exclusions will be made relating to testing or treatment for these conditions, as the same care will be available equally to women in both study arms, and the same care would be provided if either intervention were introduced into usual practice.

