## 13 Withdrawal or discontinuation of study participants

Participants will only be withdrawn from the study for the following reasons:

- Withdrawal of consent by the participant. Participants may choose to withdraw at any stage.
- Screening failure. The participant did not meet the required inclusion or exclusion criteria, and was included in the study in error
- Loss to follow-up. The participant moved out of the study area, or was lost to follow-up for some other reason.
- Death of the study participant.
- Safety reasons as judged by the safety monitor, investigator or sponsor.

A participant who chooses to withdraw from the study will always be asked for her reasons and about the occurrence of any adverse events and the reasons for her withdrawal will be recorded on the CRF.

Participants who discontinue the study drugs will not be considered withdrawn from the trial. With the participant's consent, every effort will be made to follow up those who discontinue the study drug due to adverse events in order to determine the final outcomes.

Non-adherence to the study schedule will not lead to the withdrawal of the participant unless it indicates a significant risk to her safety.

Participants who discontinue the study prematurely will not be replaced.

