### 15.1.1 Administration of the study drugs

Women in either group who attend for a scheduled study appointment with fever and malaria confirmed by RDT or microscopy will be treated for malaria. In the case of women in the IPTp-SP group, case-management treatment will be given in place of the scheduled dose of SP, and this will be recorded on the CRF.

RDTs will be performed according to the manufacturer's instructions by the study staff at the clinic. Women in the ISTp group testing positive for either *P. falciparum* or other malaria species will be treated with DHA-PQ.

Participants receiving single-dose SP or the first dose of DHA-PQ will be given some clean water for swallowing the tablets. They will be observed swallowing the tablets and for thirty minutes afterwards. If vomiting occurs during this time the full dose will be repeated. If the participant vomits again after the repeated dose she will be discontinued from the trial and provided with second line therapy for malaria (CoArtem).

Participants receiving treatment with DHA-PQ will be given the remaining doses to take home, with instructions to take half the tablets the following day and half tablets the day after. Women with mobile or home telephones will be telephoned the next day to remind them to take their next dose. Women without mobile phone will be visited at home. All women regardless of mobile phone ownership will be visited by a fieldworker on the second day to check whether they have taken the tablets and whether they have had any problems.

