## 15.2 Other treatment and concomitant medication

### 15.2.1. Routine care

All participants will be offered routine antenatal care according to local policy and the principles of 'focussed antenatal care'. This includes the provision of insecticide-treated bed nets (ITNs) free of charge.

Routine antenatal care in Malawi includes blood screening at the first appointment for syphilis, anaemia and HIV, and the provision of appropriate treatment for these conditions. Women diagnosed with anaemia or syphilis will be treated as appropriate. Women diagnosed before or during the trial as HIV-positive will be excluded or withdrawn from the

trial and offered co-trimoxazole prophylaxis. Blood screening for anaemia and HIV will also be repeated in the third trimester, as per usual care in Malawi (anaemia) and per new WHO guidelines (HIV).

As part of their antenatal care participants will be given iron and folic acid supplements (folic acid dose 0.4 mg to 0.6 mg / day) and tetanus vaccination if applicable. Helminth infections will be treated with praziquantel 40 mg / kg single dose for schistosomiasis infection, albendazole 400 mg / kg single dose for hookworm, trichuriasis and ascariasis, and albendazole 400 mg / kg per day for three days for strongyloidosis.

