## 17 Statistical methods

### 17.1 Sample size

The trial will use a stratified design with one strata for primigravidae and secundigravidae and one strata for multigravidae. It is designed to detect a 25% reduction (RR 0.75) in composite adverse birth outcomes (SGA, low birth weight and pre-term birth) in women in their first and second pregnancies with an 90% power and a 2-sided significance level of 0.05, if the rate of placental malaria in the IPT-SP group is similar to that found ongoing observational studies of women receiving routine care in the same area of Malawi. The proposed difference is based on four previous trials of IPTp which jointly reduced low birth weight by 29%. Thus the efficacy of ISTp is expected to be similar to the efficacy of IPTp before the emergence of widespread SP resistance. In the ongoing IPT-mon study in Malawi, the incidence of SGA, low birth weight or preterm birth was 40.3% (N=494) ([name], personal communication). Therefore the study is designed to detect a 25% difference between 40.3% in the control (IPTp) group and 30.2% in the intervention (ISTp) group.

This would require 491 participants in each arm or 982 in total. To allow for a 15% loss to follow-up, 1155 women in their first and second pregnancies will be recruited. This sample size would also have an 81% power to detect a 25% or greater reduction in placental malaria (active or past infection), with a significance level of 0.05. If a power of 80% is used, the study can detect a difference of 21.8% or greater in the primary endpoint. If the incidence is 33.3% instead of 40.3% the study still has 80% power (instead of 90%) to detect a 25% reduction.

The trial is also designed to detect a 50% reduction in past or present placental malaria infection at delivery in multigravidae, based on previous studies of IPTp, assessed by placental histopathology and RDT. The current rate in women in Malawi who are taking IPTp-SP is estimated from IPT-mon at 20.5% ([name], personal communication). A reduction by 50% to 10.25% will require 213 women per arm or 426 in total. To allow for a 15% loss to follow-up we will recruit 500 multigravidae.

The total sample size will therefore be  $1155 + 500 = 1655$ .

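### The primary mITT set depends on treatment received after open-label randomisation, and the vomiting and HIV rules conflict with the plan's retention and analysis sections

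*Combined protocol and SAP*

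**What the plan says.** **Primary set.** Section 17.3.3 makes the modified intention-to-treat (mITT) analysis primary for superiority. Section 17.3.1 defines mITT as women who were eligible at entry and who "received the study intervention (screening by RDT or dose of SP) on at least one occasion, with no other exclusions". Anyone who consents but leaves the same day without an RDT or SP is classed as a screening failure and not analysed. Under 16.1.1 women are randomised after consent and then told their arm.

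**Symptomatic malaria at enrolment.** Section 7.2.6 randomises these women. Those in the IPTp arm get the case-management drug, and "They will not receive SP that month"; SP follows at the next scheduled visit. Section 15.1.1 likewise replaces the scheduled SP dose. In the ISTp arm, 15.2.2 ties treatment at routine visits to a positive RDT. The per-protocol definition in 17.3.1 credits approved alternative malaria treatment; the mITT definition does not.

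**Repeat vomiting.** Section 15.1.1: "If the participant vomits again after the repeated dose she will be discontinued from the trial". Section 13 gives a closed list of withdrawal reasons. Vomiting is not named, although there is an entry for safety reasons. The same section says: "Participants who discontinue the study drugs will not be considered withdrawn from the trial".

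**HIV diagnosed during the trial.** Section 15.2.1: "Women diagnosed before or during the trial as HIV-positive will be excluded or withdrawn". Section 17.3.1: "Women who were HIV negative at enrolment but HIV positive by the third trimester will be excluded from the per-protocol analysis". Section 15.2.3 lists co-trimoxazole as prohibited medication and keeps its users in the primary analysis.

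**Missing data.** Section 17.3.7 promises effort to minimise missing data and gives no analysis method.

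**The concern.** A primary set that depends on what happens after randomisation no longer compares the groups as randomised. Here the condition is not the same in the two arms. An ISTp woman meets it by being tested. An IPTp woman must swallow SP, and the plan itself withholds SP from a subgroup with active disease. She could even qualify for per-protocol, through the alternative-treatment clause, without being in mITT. Same-day withdrawal raises a related problem, because it can follow knowledge of the arm.

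The vomiting and HIV conflicts act differently. Clinic staff following 15.1.1 and 15.2.1 would end participation; an analyst following 13 and 17.3.1 would expect a delivery outcome. If follow-up stops, the woman stays in the analysis set with nothing to analyse. The vomiting rule bears mostly on the IPTp arm, where every scheduled intervention is normally an observed dose. What is at stake is an unambiguous primary population and delivery outcomes that cannot be recovered later.

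**Working it through.** **The plan's own figure.** Section 17.1 sizes the stratum of first and second pregnancies "with an 90% power and a 2-sided significance level of 0.05", and says "the study is designed to detect a 25% difference between 40.3% in the control (IPTp) group and 30.2% in the intervention (ISTp) group". Take p1 = 0.403, p2 = 0.75 × 0.403 = 0.30225, d = 0.10075 and p̄ = 0.352625.

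- n₀ = [1.960 √(2p̄(1 − p̄)) + 1.282 √(p1(1 − p1) + p2(1 − p2))]² / d², which rounds up to 471 per arm.
- With continuity correction, n = (n₀/4)[1 + √(1 + 4/(n₀d))]² = 491 per arm, as stated. Without the correction, 491 per arm has power 0.912.
- 982/0.85 = 1,155.3, against 1,155 planned, or about 578 per arm.

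The plan gives no rates for repeat vomiting, seroconversion, same-day withdrawal or symptomatic malaria at enrolment. The rates below are assumptions.

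**1. Exposure to the vomiting rule.** IPTp: at least 3 observed doses per woman (7.2.5). ISTp: 20% to 30% of women ever treated (7.2.11), so 0.2 to 0.3 observed first doses per woman if each is treated once. Ratio: 3/0.3 = 10 to 3/0.2 = 15. If every treated woman were treated at all three visits, the ratio would be 3/0.9 = 3.3.

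**2. Women meeting the vomiting rule.** Assume v = 0.1% to 1% per observed dose, and k = 3 or 4 doses.

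- IPTp: 577.5 × [1 − (1 − v)^k] = 1.7 (v = 0.001, k = 3) to 22.8 (v = 0.01, k = 4).
- ISTp, treated once: 577.5 × 0.2 × 0.001 = 0.1 to 577.5 × 0.3 × 0.01 = 1.7.
- ISTp, 30% treated at all four visits with v = 0.01: 0.3 × 22.8 = 6.8.

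**3. IPTp women failing the dose condition.** Assume 1% to 10% are symptomatic at enrolment and 2% to 15% of those are lost before any SP: 577.5 × 0.01 × 0.02 = 0.1 to 577.5 × 0.10 × 0.15 = 8.7. There is no matching route in the ISTp arm.

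**4. Effect on the relative risk.** Remove m outcomes from 491 IPTp women, those removed having risk r. The observed control risk is (491 × 0.403 − m·r)/(491 − m).

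| m | r | Control risk | True RR 1.00 reads | True RR 0.75 reads | Power |
|---|---|---|---|---|---|
| 12 | 20% | 0.408 | 0.988 | 0.741 | 0.908 |
| 12 | 80% | 0.393 | 1.025 | 0.769 | 0.908 |
| 23 | 20% | 0.413 | 0.976 | 0.732 | 0.905 |
| 23 | 80% | 0.383 | 1.051 | 0.788 | 0.905 |

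Power is for 0.403 against 0.30225 with the IPTp arm reduced to 491 − m. Stacking both routes at their extremes (23 + 9 = 32 lost, none in ISTp) gives 0.966 to 1.074 for a true RR of 1.00, with power 0.902. This is an outer bound, since some of those 9 women would be lost to delivery follow-up under any definition.

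**5. Same-day withdrawal.** If 1% of the IPTp arm alone left this way (5.8 of 577.5), with risks of 20% to 60%, a true RR of 1.00 reads 0.995 to 1.005.

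**6. HIV.** Section 16.4.2 re-tests all women in both arms. Losing 0.2% to 2% of 491 per arm is 1 to 10 women per arm, with power 0.911 to 0.906 and no expected difference between arms.

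**The case against.** A reader might infer that the vomiting and HIV rules remove women from the primary analysis. The documents do not support that. The last clause of "received the study intervention (screening by RDT or dose of SP) on at least one occasion, with no other exclusions" keeps in mITT any eligible woman with one RDT or SP dose, and 17.3.1 excludes seroconverters from per-protocol only. The loss is indirect, through uncollected outcomes. One gap remains: the plan does not say whether a first SP dose vomited twice counts as received.

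A reader might also infer that HIV withdrawal is unequal by arm, or that the overall bias runs one way. Re-testing is the same in both arms, and nothing links infection to allocation. The direction is not established: losing high-risk controls makes ISTp look worse, and losing low-risk controls makes it look better.

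The dose-condition route is narrow. SP is due at the next scheduled visit, at least two visits remain, and 16.12 traces non-attenders. A control woman's diagnostic RDT might be read as screening. However, 15.1.1 allows RDT or microscopy, so her entry would then turn on which test was used.

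Same-day withdrawals are described as few, some may precede randomisation, and follow-up needs consent. The safety entry in section 13 might cover some vomiting or HIV cases, and 18.2 offers continued follow-up after treatment is stopped for an adverse event. These points limit the size. They do not remove the asymmetric wording or the contradictions.

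**Conclusion.** The point holds as a defect in the definition of the primary set, together with two contradictions that put outcome data at risk.

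- The mITT condition is applied after an open allocation and is asymmetric for IPTp women treated for symptomatic malaria at enrolment.
- Sections 15.1.1 and 13 conflict on repeat vomiting, under a rule to which IPTp women are exposed about 10 to 15 times as often, assuming one treatment per treated ISTp woman.
- Section 15.2.1 conflicts with 17.3.1, and sits badly with 15.2.3, on HIV. This is a contradiction, not an arm imbalance.

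The likely size is small. With up to 23 IPTp outcomes lost and risks of 20% to 80% among them, the relative risk moves by about 5% at most and power stays at or above 0.905. Both routes at their extremes together would move it by about 7%. All of this rests on assumed rates for the stratum of first and second pregnancies. The planned sample size reproduces and does not change. The reason to act is that the primary population should be unambiguous and delivery outcomes should not be lost for want of clear wording.

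**What to change.** 1. In 17.3.1, define the primary set as all randomised women analysed as allocated. Exclude only women shown, blind to arm and from facts fixed before randomisation, to have been ineligible (a missed twin pregnancy, for example). At minimum, count approved alternative malaria treatment as the intervention for mITT, as per-protocol already does.
2. State that a woman who stops study drug for any reason is, with her consent, followed to delivery and kept in the primary analysis.
3. In 17.3.7, name a method for missing delivery outcomes and a sensitivity analysis that lets the risk among missing women differ by arm.
4. Have the trial team reconcile sections 13, 15.1.1, 15.2.1, 15.2.3 and 17.3.1 so that clinic staff and analysts treat the same woman alike. No clinical rule is proposed here.

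The cost is a wording amendment, a few extra delivery follow-ups within the existing tracing system, and slight dilution from a few women who never had the intervention. The requirement of 491 per arm is unchanged.

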### 6.2.3 Modifiers of efficacy

To explore the possibility of differences in treatment effect by gravidity (first or second pregnancy versus third or subsequent pregnancies) or other groupings relating to the risks of malaria in pregnancy, such as malaria transmission season, location, age, number of intervention visits.

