### 17.3.3 Efficacy

The primary efficacy analysis will be the assessment of the superiority of ISTp-DP over IPTp-SP in women in their first and second pregnancies for the prevention of any of the following: SGA, pre-term birth or low birth weight. Similar analyses will be undertaken for the additional primary outcome of evidence of active or recent infection assessed at delivery by placental histopathology and RDT in women in their third to fifth pregnancies, and for the secondary efficacy outcomes. Impact will be determined by gravidity strata as the primary analysis. As a secondary analysis we will also estimate the overall estimated effect, extrapolated to all gravidity groups using a weighted analysis providing extra weight to the observations in multigravidae so that the final estimate represents the distribution of gravidity groups in the population attending antenatal clinics (based on antenatal clinic records).

Generalised linear models will be used where appropriate to assess the effect of the intervention according to different characteristics of the participants. Treatment effects will be expressed in terms of relative risk and risk difference for dichotomous variables and mean difference for continuous variables, and the corresponding 95% confidence intervals. Superiority will be defined as a positive treatment effect that is greater in the ISTp group than the IPTp group, where the 95% confidence interval does not include the point of no difference (RR value of 1).

Both modified intention-to-treat and per-protocol analyses will be undertaken for the efficacy analyses. The modified intention to treat analysis will be the primary analysis to assess superiority. In the absence of evidence for superiority, the prospectively defined non-inferiority margin will be 15% for adverse outcome or placental malaria in the intention to treat and per protocol populations (relative difference between endpoints of 15% (i.e. RR 0.85); e.g. 24.5% versus 28.8% for adverse birth outcome).

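### The per-protocol rule lets a woman's outcome, or an early birth, decide whether she stays in after fewer than three interventions, in a set to which the non-inferiority margin is applied

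*Combined protocol and SAP*

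**What the plan says.** Section 17.3.1 gives three routes into the per-protocol set for women who met the entry criteria.

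1. The intervention was received "on at least three separate occasions at least four weeks apart".
2. The route at issue: "or reached a study end-point before completion of the three-visit schedule but received the intervention at least once".
3. Replacement treatment: "or received an approved alternative treatment for symptomatic malaria according to protocol that replaced the need for the scheduled intervention". Section 15.1.1 shows how this arises in the IPTp-SP arm, where for febrile women with confirmed malaria "case-management treatment will be given in place of the scheduled dose of SP".

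Section 17.3.1 does not define a study end-point. The Synopsis, section 7.2.10 and section 9.1 use endpoint for the outcomes themselves: small for gestational age, low birth weight or preterm birth in first and second pregnancies, and malaria infection at delivery in later ones.

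Section 17.3.3 makes modified intention to treat primary for superiority. If superiority is not shown, "the prospectively defined non-inferiority margin will be 15% for adverse outcome or placental malaria in the intention to treat and per protocol populations". It does not say whether both populations must meet the margin.

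Section 6.2.3 lists possible effect modifiers, "such as malaria transmission season, location, age, number of intervention visits".

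**The concern.** Take two women who each received two interventions and no replacement treatment. On the broad reading of the second route, the one whose baby is small for gestational age stays in the per-protocol set and the one with a healthy baby is removed.

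The narrow reading takes the timing words seriously: the route covers only pregnancies that ended before the schedule was complete. The final intervention visit is at 34 to 37 weeks (section 16.4) and preterm birth is birth before 37 weeks (section 9.1). The women kept are therefore mostly events, and they are kept even if they had already missed visits that fell due. Women with the same attendance who delivered later are dropped.

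Selection of this kind raises the per-protocol event rate in both arms. If completion differs between arms, it raises the two rates by different amounts. The open-label design makes a gap possible, though nothing in the documents predicts its size or direction. The stake is the non-inferiority assessment.

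The section 6.2.3 point is related. The number of visits attended is determined after randomisation and is cut short by preterm birth, a component of the primary endpoint. A subgroup formed on it is not protected by randomisation.

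**Working it through.** **Inputs from the documents.** Section 17.1: control rate 40.3% in first and second pregnancies, 491 per arm. Section 17.3.3: margin stated as "relative difference between endpoints of 15% (i.e. RR 0.85); e.g. 24.5% versus 28.8% for adverse birth outcome". For a harmful outcome expressed as ISTp/IPTp, this is taken here as 1/0.85 = 1.176; the plan does not state the direction.

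**Reproducing the plan's figure.** With 40.3% against 0.75 × 40.3%, two-sided 0.05, 90% power and a continuity correction, the two-proportion formula gives 491 per arm, as stated. Without the correction it gives 469 to 471.

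**Assumptions.** Completion share a (three interventions) is between 75% and 95% per arm; the documents give none. Completion is unrelated to outcome before the rule is applied. For the narrow reading, 8% of women deliver before the last visit and all of these are events.

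**Broad reading, no true effect.** All completers are kept, plus non-completers with an event, so the per-protocol rate = p / [p + (1 − p)a], with p = 0.403.

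- a = 0.85: 0.403 / (0.403 + 0.597 × 0.85) = 0.403/0.9105 = 44.3%
- a = 0.75: 0.403 / (0.403 + 0.597 × 0.75) = 0.403/0.8508 = 47.4%
- Equal completion: ratio 1.00
- 85% IPTp, 75% ISTp: 47.4/44.3 = 1.07. Reversed: 0.93

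On the log scale, 1.07 is ln 1.07 / ln 1.176 = 0.0677/0.1625 = 42% of the margin.

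**Broad reading, true ratio at the margin, 85% completion in both arms.** The ISTp rate is 0.403/0.85 = 0.474. Its per-protocol rate is 0.474 / (0.474 + 0.526 × 0.85) = 51.5%, and 51.5/44.3 = 1.163 rather than 1.176. Equal completion therefore pulls a real disadvantage toward 1.

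**Narrow reading, no true effect.** With e = 0.08 and other events 0.403 − 0.08 = 0.323, rate = (e + 0.323a) / (e + 0.92a).

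- a = 0.85: 0.3546/0.862 = 41.1%
- a = 0.75: 0.3223/0.770 = 41.9%
- Ratio 1.017 (reversed, 0.983)
- Dropping the early births altogether: 0.323/0.92 = 35.1%, further from the true 40.3%

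**Decision rates, broad reading.** Simulation with 491 per arm, 200,000 runs, 95% confidence interval on the log risk ratio, margin 1.176. Non-completion is shown as IPTp/ISTp.

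| True ratio | Non-completion | Per-protocol meets margin | Modified ITT meets margin | Both |
|---|---|---|---|---|
| 1.176 | 15%/15% | 3.8% | 2.6% | 2.3% |
| 1.176 | 15%/10% | 8.2% | 2.5% | 2.5% |
| 1.176 | 20%/10% | 18.2% | 2.6% | 2.6% |
| 1.00 | 15%/15% | 58.1% | 55.2% | 52.5% |
| 1.00 | 10%/20% | 25.4% | 55.4% | 25.4% |

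With no true effect and 10%/20% non-completion, a per-protocol difference significantly against ISTp appears in about 14% of trials, against a nominal 2.5%. In the same scenarios, a completers-only set and an all-women set give a ratio of 1.00.

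**The case against.** The strongest case against is that the route has a sound purpose. A woman enrolled at 28 weeks, with visits at least four weeks apart, cannot have a third before 36 weeks, so preterm birth can make completion impossible. Removing such women would discard events: on the inputs above, the rate falls to 35.1% without them, against 41.1% to 41.9% with the route. The timing words also favour the narrow reading, under which the distortion is about 2%. This stands, and it is why the route should be rewritten rather than deleted. It does not cover women who had already missed visits before an early birth, and it does not supply the missing definition.

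A reader might infer more than the documents support:

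- That women with fewer than three interventions stay only if they had an endpoint. The replacement-treatment route needs none.
- That the rule creates a spurious difference by itself. With no true effect, that needs unequal completion. Follow-up of non-attenders (section 16.12) and travel reimbursement (section 7.1) apply to both arms. The extra contacts for women treated with DHA-PQ (sections 16.5 and 16.6) would, if anything, raise ISTp attendance, and only 20% to 30% of ISTp women are expected to be treated (section 7.2.11).
- That the superiority conclusion is compromised. It rests on modified intention to treat, which has no such clause.
- That the rule alone can deliver a false non-inferiority finding. It can do so only if the per-protocol result may stand by itself.
- That section 6.2.3 is plainly wrong. Its wording can mean the planned three or four visits, which follow gestation at enrolment (section 16.3), and the analysis is exploratory.

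**Conclusion.** The point holds in limited form. Per-protocol membership for women with fewer than three interventions depends on the outcome on the broad reading, and on early, mostly preterm birth on the narrow one.

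For first and second pregnancies, a 10-point completion gap gives a spurious ratio of about 0.93 to 1.07 on the broad reading and about 1.02 on the narrow reading if ISTp completes less. With equal completion there is no spurious difference under no effect. A true difference is diluted, which is anti-conservative for non-inferiority. All of this rests on assumed completion shares and, for the narrow reading, on the assumed 8%.

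If both populations must meet the margin, false non-inferiority stays near 2.5%, and the main harm is the opposite error: with equal true risks and 10%/20% non-completion, the chance of meeting it in both sets is about 25%, against about 55% in modified intention to treat alone. The issue deserves correction before analysis but does not threaten the primary superiority result.

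**What to change.** In section 17.3.1, replace the second route with: received every scheduled intervention that fell due before the pregnancy ended, whatever the birth outcome. For women who reached the final-visit window, keep at least three interventions at least four weeks apart as sufficient, including for those with four planned visits; otherwise women attending three of four would be newly excluded. Count replacement treatment given under the protocol as attendance.

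State that this set still depends on gestation length, so it reduces the selection without removing it and is to be read alongside modified intention to treat. In section 17.3.3, say whether the margin must be met in both populations and give its direction as an ISTp/IPTp ratio.

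In section 6.2.3, use gestational age at enrolment (16 to 23 against 24 to 28 weeks) or the planned number of visits, not visits attended.

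The cost is analysis-plan wording and a somewhat different per-protocol set size. Visit and delivery dates are already collected.
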